
The health impacts of climate change are primarily driven by rising temperatures and increased heat exposure, which are projected to contribute to a surge in heat-related morbidity and mortality, including conditions such as heat stress, cardiovascular diseases, and renal dysfunction [9]. Additionally, climate change is expected to exacerbate the burden of communicable diseases such as dengue fever, pathogenic *Vibrio* infections, and malaria, as warmer and more humid conditions enhance the suitability for vector proliferation and disease transmission [9]. Changes in rainfall and temperature patterns are likely to affect mosquito breeding cycles, further increasing malaria risk [9]. Notably, malaria, pneumonia, and diarrheal diseases together account for nearly half of all deaths in children under five in sub-Saharan Africa (SSA) [27]. In the Kossi region of northwestern Burkina Faso, shifting seasonal weather patterns, rising temperatures, and extreme weather events, including heavy rainfall and flooding, have been associated with direct health impacts, including increased incidences of heatstroke and malaria, as well as indirect effects such as heightened food insecurity and child undernutrition [3,28–32]. In both Burkina Faso and Kenya, climate change exacerbates child undernutrition by compromising food security [30,33,34]. The increasing frequency of severe weather events, such as droughts and floods, reduces crop yields and elevates food prices, leading to inadequate dietary intake and heightened health risks associated with undernutrition [30,33,34]. Chronic undernutrition affects 26% of children under five in Burkina Faso and over 25% in Kenya, contributing to stunting, while acute undernutrition leads to wasting in about 7% of children in Burkina Faso and 4% in Kenya. These conditions have long-term consequences for cognitive and physical development [30]. Moreover, exposure to drought during late childhood and early adolescence has been shown to have persistent adverse effects on growth, primarily mediated by reduced nutritional intake during critical developmental years [35]. In Burkina Faso, studies have demonstrated that rainfall variability directly impacts crop yields and correlates with increased child undernutrition in affected households [36,37].

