**What is the impact of heat exposure on the physiological responses of farmers?**
**Hypothesis 1**: Increased heat exposure will significantly elevate physiological strain, as measured by heart rate and body temperature.**How does heat exposure influence farmers’ work capacity and farming behaviors?**
**Hypothesis 2**: Higher temperatures will reduce work capacity and alter farming behaviors, including daily activity patterns, sleep quality, duration, and energy expenditure.**What is the relationship between heat exposure, work capacity, health, and farming practices on harvest yields?**
**Hypothesis 3**: Heat exposure will lead to reduced harvest yields by impairing farmers’ work capacity and health.**How do these factors indirectly affect the nutritional status of children under five in farming households?**
**Hypothesis 4**: Reduced work capacity and lower harvest yields due to heat exposure will negatively impact child nutrition.

This study systematically investigates these pathways using wearable sensors, GPS tracking, offering valuable insights into climate-related challenges faced by subsistence farmers and their families.

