The fourth health impact pathway addresses the indirect consequences of heat-induced agricultural disruptions on child nutrition. Declining crop yields and increasing food insecurity may lead to dietary deficiencies, heightened undernutrition, and associated health risks in children under five. By linking environmental stressors to household food availability, this pathway seeks to quantify the nutritional and health impacts of heat exposure on vulnerable populations.

A conceptual framework (refer to Figures 1 and 2 for the conceptual framework of the H2H study and its pathways) illustrates the relationships between heat exposure, physiological strain, agricultural productivity, and child nutrition. The study will incorporate controls for potential confounders to ensure that observed effects can be robustly attributed to heat exposure rather than external factors such as soil fertility, rainfall variability, or market fluctuations.

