#### Nutritional status (health impact pathway 4)

Anthropometric measurements, including weight and height assessments of children under five years of age, will be used to identify those with poor nutritional status. Nutritional classification will follow the World Health Organization (WHO) Child Growth Standards, where chronic undernutrition (stunting) is defined as a height-for-age z-score (HAZ) ≤ −2.0, and acute undernutrition (wasting) as a weight-for-height z-score (WHZ) ≤ −2.0, adjusted for age and sex [50].

To assess the relationship between heat exposure and child nutritional status, chi-square tests will first be used to evaluate unadjusted associations associations between categorical heat exposure levels and the prevalence of stunting and wasting. To estimate the independent effect of heat exposure on child growth outcomes, multivariate logistic regression models will be employed, adjusting for potential confounders such as household socioeconomic status, dietary intake, and recent illness episodes. To ensure the robustness of these findings, sensitivity analyses will be conducted to control for key confounding factors, including household socioeconomic status, dietary intake, and recent illness episodes. These additional analyses will allow for a more accurate estimation of the independent effect of heat exposure on child growth outcomes, strengthening causal inference within the broader analytical framework.

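### The child-nutrition regression adjusts for dietary intake as a confounder, although the protocol's own pathway makes it a mediator, so it does not estimate the total effect of heat

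*Protocol article*

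**What the plan says.** All references are to the protocol article.

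- **Target.** Data analysis, Nutritional status (health impact pathway 4): "To estimate the independent effect of heat exposure on child growth outcomes, multivariate logistic regression models will be employed".
- **Adjustment set.** The same sentence continues: "adjusting for potential confounders such as household socioeconomic status, dietary intake, and recent illness episodes".
- **Sensitivity analyses.** Same section: "sensitivity analyses will be conducted to control for key confounding factors, including household socioeconomic status, dietary intake, and recent illness episodes". These are the same three variables. The only analysis in that section without diet is an unadjusted chi-square test, which also leaves out socioeconomic status (SES).
- **Causal model for diet.** Methods, fourth health impact pathway: "Declining crop yields and increasing food insecurity may lead to dietary deficiencies, heightened undernutrition, and associated health risks in children under five". The Background says that severe weather "reduces crop yields and elevates food prices, leading to inadequate dietary intake and heightened health risks associated with undernutrition".
- **Hypothesis 4.** "Reduced work capacity and lower harvest yields due to heat exposure will negatively impact child nutrition". It names neither diet nor illness.
- **Illness.** The Background lists, as consequences of weather change, "direct health impacts, including increased incidences of heatstroke and malaria, as well as indirect effects such as heightened food insecurity and child undernutrition".
- **Related text.** The section on structural equation modeling (SEM) plans direct, indirect and total effects of heat on child nutrition. The Data analysis section says that a DAG will be built. Expected results counts household food access among the confounders to be controlled.

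**The concern.** A variable that transmits the effect of an exposure cannot also be treated as a confounder of it when the aim is the overall effect. The article assigns dietary intake both roles. Adjusting for it closes part of the route that the study sets out to examine, and what remains is at best a residual direct effect.

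Conditioning on a mediator also opens paths through unmeasured household factors that influence both diet and growth. The residual is then not a clean direct effect unless those factors are dealt with, and the section does not mention them.

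Three things are at stake. The section presents the result as strengthening causal inference. It could disagree with the total effect from the SEM, and no rule says which one to report. Expected results also plans exposure–response functions linking heat to child nutrition for use in impact models, and an attenuated estimate could be carried into those.

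**Working it through.** **1. Plan's own figure.** There is none for child nutrition. The only computed design figure, 63 per group, concerns heart rate and has no bearing here.

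**2. Role of each adjusted variable, from the text alone.**

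| Variable | Role in the regression | Role in the causal text |
|---|---|---|
| Household SES | confounder | background factor; no conflict if measured at baseline |
| Dietary intake | confounder | step between yield loss and undernutrition (fourth pathway; Background) |
| Recent illness | confounder | malaria and heatstroke are climate effects listed beside undernutrition; not shown as a step to it |

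The contradiction is explicit for diet and only possible for illness.

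**3. Size on a linear scale.** Let m be the share of the total heat effect T that passes through diet. With no unmeasured common cause, the diet-adjusted coefficient is T × (1 − m). So m = 25%, 50%, 75% or 100% leaves 75%, 50%, 25% or 0% of the effect. The documents give no value for m.

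**4. Illustration on the odds-ratio scale.** This is a simulation of 400,000 children. All coefficients are assumed: total heat effect −0.20 on a latent growth score per SD of heat, lowest 26% classed as undernourished, SES affecting heat, diet, illness and growth, and heat affecting diet (−0.4) and illness (0.3). The last two columns add an unmeasured cause U of both diet and growth (0.4 on each). Entries are odds ratios for heat.

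| Via diet | Via illness | SES only | SES + diet + illness | With U: SES only | With U: SES + diet + illness |
|---|---|---|---|---|---|
| 0% | 0% | 1.45 | 1.45 | 1.41 | 1.24 |
| 25% | 0% | 1.46 | 1.33 | 1.40 | 1.14 |
| 50% | 0% | 1.44 | 1.21 | 1.38 | 1.04 |
| 50% | 25% | 1.44 | 1.10 | 1.38 | 0.95 |
| 75% | 0% | 1.43 | 1.09 | 1.35 | 0.94 |
| 75% | 25% | 1.42 | 0.99 | 1.35 | 0.86 |
| 100% | 0% | 1.41 | 1.00 | 1.35 | 0.87 |

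Check against step 3: at 50% through diet, ln 1.21 / ln 1.44 = 0.191 / 0.365 = 0.52, close to the expected half.

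Without U, adjustment does nothing when nothing is mediated, attenuates under partial mediation, and removes the effect only under complete mediation. With U, the adjusted estimate moves even when nothing is mediated (1.41 to 1.24), and it can cross 1.

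**5. Separate matter: the −2 cut.** For a normally distributed z-score, dichotomising at prevalence p keeps φ(z)² / [p(1 − p)] of the information, where z is the normal quantile of p. The Background gives stunting of 26% in Burkina Faso and over 25% in Kenya, and for wasting "acute undernutrition leads to wasting in about 7% of children in Burkina Faso and 4% in Kenya".

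| p | Information kept |
|---|---|
| 0.26 | 0.55 |
| 0.25 | 0.54 |
| 0.07 | 0.28 |
| 0.04 | 0.19 |

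**The case against.** **The total effect is handled elsewhere.** The SEM is to estimate it, and the regression's independent effect could be read as a direct effect. This stands in part: the cascade is not lost from the study. But the regression section calls these variables confounders, not mediators held fixed, and does nothing about common causes of diet and growth. The SEM's example paths do not include diet, so they do not explain the adjustment either.

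**The covariate list is illustrative and a DAG is to come.** True, but the article names dietary intake twice, in the main and the sensitivity models, and this conflicts with the pathway it has already described. That is a stated choice, not a detail left to a fuller document.

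**Timing.** Children are measured at the start of the harvest season, while wearables run during it, so diet recorded at that visit can mediate only earlier heat. This is fair, and the heat window needs defining. It does not restore diet as a confounder: only earlier heat can affect that measurement, and the fourth pathway puts diet after heat-related yield loss.

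**Illness.** A reader might infer that illness is an established mediator. The documents do not support that. Malaria is tied to rainfall as well as temperature and stands beside undernutrition, not before it, so illness may partly stand in for a confounder.

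**Cut-offs.** The WHO thresholds are the classification the section adopts, and they give prevalence. Using them is not an error. Table 1 lists weight and height as continuous and does not mention z-scores.

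**Conclusion.** The adjustment set is wrong as written for dietary intake. The regression does not estimate the total effect of heat on child nutrition, and the sensitivity analyses cannot reveal this. The attenuation is proportional to the share passing through diet, which the documents do not give. The odds ratios above rest on assumed coefficients and show only the pattern.

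Three stronger readings are tempting but not supported:

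- **The model removes the effect.** That requires complete mediation.
- **The bias is always toward zero.** Unmeasured common causes can carry the estimate past 1, so the direction is uncertain.
- **The model conditions on the steps named in Hypothesis 4.** That hypothesis names work capacity and yield, and neither is among the adjusted variables. The diet step comes from the fourth pathway and the Background.

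This should be fixed before analysis. It is not of the highest severity, because the primary outcome is heart rate, this is a feasibility phase, and the SEM already targets total effects.

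**What to change.** 1. State the estimand of the child-nutrition regression (total or direct effect) and the heat window that precedes the anthropometry.
2. For the total effect, adjust only for pre-exposure covariates, such as baseline SES and child age and sex. Choose site and year terms with care: with five weather stations per site and three years, they may absorb much of the variation in outdoor heat.
3. Use diet as a mediator in the SEM, and illness too if the planned DAG supports it.
4. Make the sensitivity analysis the comparison with and without these variables.
5. Reconcile the fourth pathway, the SEM section, the nutritional-status section and Expected results, where household food access is also called a confounder.

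The cost is analysis-plan wording; no new data are needed.

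As a separate, cheap improvement, analyse height-for-age and weight-for-height z-scores as continuous outcomes alongside stunting and wasting. Under normality the cut keeps about 54–55% of the information at 25–26% prevalence and 19–28% at 4–7%. The downside is that prevalence odds ratios become secondary.

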#### Work capacity and physiological response (health impact pathway 2)

To further quantify the relationship between heat exposure and farmers’ work capacity, we will apply a combination of regression models and machine learning techniques. These approaches complement the broader analytical framework by enabling the detection of both linear and non-linear associations between environmental conditions and physiological responses.

Key heat exposure variables – indoor and outdoor temperature, humidity, and Wet Bulb Globe Temperature (WBGT) – will be modeled against continuous physiological indicators such as heart rate, activity levels, and sleep patterns. Linear mixed-effects models will be used to account for within-subject variability and repeated measures, with random effects specified at the individual level to capture heterogeneity in exposure and response. These models will incorporate covariates such as socioeconomic status and farming intensity to control for confounding.

Model validation will involve standard diagnostic tools including residual and Q – Q plots to assess normality, and Variance Inflation Factor (VIF) analysis to detect multicollinearity. In parallel, cross-validation and residual error analysis will be employed to test model robustness and predictive accuracy. Sensitivity analyses will explore how natural variations in environmental conditions – particularly fluctuations in temperature and humidity – affect the stability and reliability of the modeled outcomes.

To enhance the physiological assessment of energy expenditure and physical effort, we will deploy the Renkforce GP-102 GPS Logger, which includes an integrated pedometer function. These devices will collect location and movement data every 15 minutes, allowing for the estimation of energy expenditure based on distance traveled, travel speed, terrain changes, and rest intervals.

Time spent in agricultural fields will be georeferenced, with GPS data linked to each participant’s unique ID and merged with socio-demographic characteristics, field boundaries, and movement patterns. This enables a comprehensive analysis of how mobility and environmental exposure interact to shape work capacity.

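### The child-growth sensitivity analysis names the same three covariates as the main logistic model, so as written it repeats that model and cannot support the claim of stronger causal inference

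*Protocol article*

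**What the plan says.** The relevant text is in the protocol article, Data analysis, under Nutritional status (health impact pathway 4). It has three steps.

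- Chi-square tests give unadjusted associations between categories of heat exposure and stunting or wasting.
- Logistic regression then estimates the independent effect of heat, "adjusting for potential confounders such as household socioeconomic status, dietary intake, and recent illness episodes".
- To show that these findings are robust, "sensitivity analyses will be conducted to control for key confounding factors, including household socioeconomic status, dietary intake, and recent illness episodes".

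The paragraph closes with what the third step is meant to achieve: "These additional analyses will allow for a more accurate estimation of the independent effect of heat exposure on child growth outcomes, strengthening causal inference".

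Elsewhere the article names factors that neither list mentions. The opening of Expected results counts farm size and household food access among the potential confounders to be accounted for. The Discussion, under Child undernutrition, says maternal health will be considered.

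**The concern.** A sensitivity analysis is useful because it changes something the main result might depend on, and so could give a different answer. Here the second and third steps name the same adjustment set, and no other element is said to change. The check would therefore agree with the main model however fragile that model is.

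What is at stake is how the result is read. Agreement could be reported as robustness, and the article has already said that it strengthens causal inference. The estimates are meant to travel: under Expected results, the exposure-response functions linking heat to child nutrition are offered as inputs to climate impact models. Readers of those functions would believe that confounding had been probed when it had not.

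**Working it through.** The article gives no figure to reproduce here, so the check compares the two descriptions and follows the consequence.

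**Step 1. The two analyses side by side**

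| Element | Main logistic model | Sensitivity analysis |
|---|---|---|
| Socioeconomic status | named | named |
| Dietary intake | named | named |
| Recent illness | named | named |
| Farm size, food access, maternal health | not named | not named |
| Different outcome coding, exposure definition, children analysed or model form | – | none stated |

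Among the named covariates, nothing is in one set and not in the other.

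**Step 2. What follows for the estimate**

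The model is logit P(Y = 1) = a + b·heat + c1·SES + c2·diet + c3·illness. With the same outcome, exposure, children and covariates, the likelihood is the same function and has the same maximum. Hence b(sensitivity) − b(main) = 0, and the standard errors and intervals coincide. As a numerical confirmation, 200 simulated data sets of 2,000 children (assumed inputs) were each fitted twice with the same three covariates in a different order. The largest difference in the log odds ratio for heat was about 1e-16, which is rounding error.

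**Step 3. What follows for bias**

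Let B be any bias in the main estimate from a factor outside the three covariates. The main analysis estimates b + B, and so does the sensitivity analysis. Their difference is (b + B) − (b + B) = 0 for every value of B. Observing agreement therefore says nothing about B. The article gives no basis for a value of B, and none is assumed here.

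**Step 4. Whether the named covariates are themselves beyond question**

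The fourth pathway, in the Methods section on health impact pathways, runs from falling yields and food insecurity to dietary deficiency and undernutrition. The section on structural equation modeling specifies a path from heat through work capacity and yield to child nutrition. Diet may therefore lie on the path from heat to growth, so adjusting for it may remove part of the effect under study. Recent illness may raise the same question, since the Background links warmer conditions to more infectious disease. A comparison with and without these two covariates could give a different answer, which the planned check cannot.

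**The case against.** The strongest defence is that both lists are open. The main model's covariates are given as examples, and the sensitivity list as a partial one. The opening of Data analysis also plans a directed acyclic graph of confounding factors. A full protocol or analysis plan, not shown, may give two different sets. This stands in part: identity is shown only for the covariates named. But the article chose to describe the check, the only content it gave duplicates the main model, and it attached a causal claim to that content. This is a stated analysis without its stated property, not omitted detail.

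The repetition may also be an editing slip. The section on anthropometric measurements states the timing of measurement twice in nearly the same words. If the third step merely restates the second, there is no sensitivity analysis here at all, and the claim still needs correcting. The possibility bears on seriousness, not on whether to change the text.

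A reader might extend the point to the heat models under Work capacity and physiological response (health impact pathway 2), where "Sensitivity analyses will explore how natural variations in environmental conditions". Temperature and humidity are exposures in those models, so this too may look empty. The documents do not support that reading. The stated aim is only to see how such variation may "affect the stability and reliability of the modeled outcomes", with no causal claim. The wording is loose enough to cover refits over different temperature or humidity ranges, which could show instability. Cross-validation and residual analysis are planned beside it.

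**Conclusion.** The point holds for the child-growth analysis. If the adjustment sets are the three covariates named, the sensitivity estimate equals the main estimate exactly. It can then neither improve accuracy nor strengthen causal inference. The conclusion rests on reading the two lists as printed and on no other unstated difference between the analyses.

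Its reach is limited. Child growth is the fourth, downstream pathway of a study in its feasibility phase, the primary outcome is heart rate, and no sample size depends on this. A reader might infer that the heat estimate for child growth is confounded, or by how much. The article gives nothing from which to establish either. What is shown is that the check could not detect such a problem.

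**What to change.** Replace the sensitivity sentence with analyses that differ from the main model and can disagree with it:

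- **(a)** The heat estimate with and without dietary intake and recent illness, stating that diet may lie on the pathway from heat through yield and food to nutrition.
- **(b)** The main model with farm size and maternal health added. Food access should be added only as a separate variant, read as possibly blocking part of the effect.
- **(c)** Optionally, an E-value for the heat estimate. Stunting affects about a quarter of children according to the Background, so the odds ratio should first be converted to an approximate risk ratio.

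Fit all variants to the same children, so that a change is not due to missing covariates. Compare them as standardised risk differences, or with the z-scores as continuous outcomes, because an odds ratio can shift when covariates are added even without confounding.

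If heat after the anthropometry visit is used as a negative control, heat before the visit must be in the same model. The two are likely to be correlated, and an association with later heat alone would not show confounding.

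If none of this is adopted, withdraw the statements about more accurate estimation and stronger causal inference.

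The cost is a change of wording and a little more analysis, using factors the article already says it will consider. The robustness statement may also turn out less firm.
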